## Abstract

**Introduction:**

Firefighters, compared to other occupational groups, are exposed more frequently in their working environment not only to physical issues, such as musculoskeletal disease, respiratory disease, and burns but also to mental health issues, such as PTSD and depression. Specifically, Korean firefighters experience significantly higher rates of work-related injuries compared to those in other countries. Recent statistics from the Korea National Fire Agency indicate a steady increase in the number of firefighting work-related injuries. However, there is a shortage of measures in place to address these issues. This study aims to investigate the health needs, overall healthcare usage, and unmet needs of firefighters in Korea. We also aim to investigate, through in-depth interviews, perceptions and hindering factors for integrative medicine approaches to fulfilling unmet needs.

**Method:**

This study was conducted in accordance with the consolidated criteria for reporting qualitative research. Convenience and snowball sampling methods will be used to recruit firefighters to participate in the study, and interviews will be conducted using a semi-structured interview guide. The data will be analyzed in four stages using the qualitative analysis method of Krippendorff.

**Discussion:**

In this study, we examine the state of health issues and healthcare usage among Korean firefighters and investigate their perceptions of and needs for integrative medicine. In this way, we aim to explore how integrative medicine and Korean medicine approaches could improve and assist healthcare services for firefighters. Furthermore, our findings will provide policymakers and healthcare providers with the necessary basic information to develop integrative medicine systems suited to firefighters.

## Introduction

Firefighters are exposed to hazardous environments that can cause both physical harm and psychological trauma by the nature of their jobs [1, 2]. In Korea, firefighters are civil servants who work at fire service facilities, including fire stations, fire and safety departments, and the Korea National Fire Agency, performing various fire service-related tasks, including fire prevention, fire safety monitoring, firefighting, and rescue [3]. Due to the nature of their work, firefighters are at risk of various diseases due to exposure to environmental risk factors and hazards [4]. Also, the work-related injuries rate among Korean firefighters is noticeably higher than that of firefighters in other countries. According to recent statistics from the Korea National Fire Agency, the number of injuries related to firefighting work has steadily increased over the past 10 years [5, 6]. First, respiratory diseases, such as pneumonia, asthma, and chronic obstructive pulmonary disease (COPD), are common among firefighters, due to exposure to smoke and other harmful substances [7]. Second, there is a risk of skin injury due to burns and exposure to chemical substances [8]. Third, carrying equipment, performing rescues, and other physically challenging tasks lead to a high incidence of spine and joint disorders [9]. Finally, firefighters can experience heavy stress at accident sites, causing emotional problems such as depression, anxiety disorder, and post-traumatic stress disorder (PTSD) [10].

In the United States, which has good welfare for firefighters, standard guidelines (NFPA 1583) from the National Fire Protection Association (NFPA) propose more systematic wellness/fitness programs for the safety, health management, and welfare of firefighters [11]. Meanwhile, they provide care programs for mental health issues like PTSD through peer support, where firefighters with expertise in psychiatric counseling provide counseling directly. However, even though the importance of health improvements for firefights has been emphasized, and there have been studies on the effects of health management programs, these programs are still not being implemented at over 70% of fire stations, leading to a shortage of actual care with regard to health management for firefighters [12].

In Korea, the National Fire Agency runs various mental health programs for firefighters, including managing work stress, managing PTSD, improving motivation for learning, and self-management [13]. However, the programs are of poor quality and are not systematic [14]. According to a study on the state of health management programs for emergency responders, although most facilities (88.3%) were running health management programs involving physical training facilities and special lectures, satisfaction was not high [15]. Thus, although various efforts are being made at the national level to manage the physical and mental health of firefighters, there are still unmet needs, especially for pain, rehabilitation, burns, and psychological issues, such as PTSD [16]. To resolve the unmet needs of firefighters regarding health problems, it is necessary to determine these unmet needs and devise measures to fulfill them.

In East Asia, various types of traditional medicine are used for health issues [17], and in Korea, civil servants also utilize Korean Medicine(KM) for health issues [18]. In South Korea’s binary Western/Korean healthcare system, because KM treatments are included in the National Health Insurance Service, accessibility is relatively high, and for patients’ convenience and effective treatment, integrative medicine is often provided as a form of collaborative care [19, 20]. Several systematic literature reviews have reported positive effects of KM on conditions commonly experienced by firefighters, including musculoskeletal pain [21], postoperative pain management [22], respiratory problems [23], digestive problems [24], headache [25], depression [26], and PTSD [27]. Therefore, KM can play a role in supporting their health and well-being in several ways.

However, studies on the unmet health needs of firefighters or the potential role of KM in these issues are lacking. Moreover, there is an insufficient in-depth understanding of Korean firefighters’ overall healthcare utilization; thus, it remains unclear what the expectations and obstacles are for integrative medical approaches. Therefore, we plan to conduct a study aimed at investigating Korean firefighters’ health needs, overall healthcare usage, and unmet needs to generate useful data supporting personalized improvements in healthcare services for Korean firefighters. Our findings will provide policymakers and healthcare providers with the necessary basic information to develop integrative medicine systems suited to firefighters.

## Materials and methods

### Objectives

The primary objective of this study is to gain an in-depth understanding of the unmet needs of Korean firefighters regarding healthcare utilization, from the firefighters’ perspective.

The secondary objective is to examine what experiences Korean firefighters have of integrative medicine, obstacles to its use, and how it could help with their unmet needs.

### Study design

In this qualitative study, we use content analysis to explore overall content on the state of healthcare utilization by Korean firefighters and their perceptions and needs regarding KM. This study will be performed in accordance with the consolidated criteria for reporting qualitative research (COREQ) [28]. We provide COREQ checklist (S1 Checklist), the Korean version of the full protocol (S1 File), and English version of full protocol (S2 File).

### Sample size

To ensure the validity of this study, we will use a sample size of 20 persons, which is the suggested sample size for qualitative research [29].

However, after interviewing 20 persons, the researchers can perform additional interviews if they feel the data is not yet saturated.

Saturation is a criterion for stopping data collection, referring to the state where no new data is being discovered from new participants, and so no further qualitative interviews are required.

### Participant recruitment

Recruitment is scheduled to commence on October 4, 2023, and conclude on December 31, 2024. Participants will be recruited using two different methods. First, using convenience sampling, with cooperation from the Korea National Fire Agency, we will recruit participants via an official notice posted to the internal intranet. We will then use snowball sampling to recruit other participants. This is a non-probability sampling method, where other participants are recruited through referral by previous participants; this is an effective method for studying relatively inaccessible populations [30]. The inclusion criteria are Korean firefighters aged 19–65 years who voluntarily consent to participate in the study. Considering that 19 years old marks the legal age of adulthood in South Korea, we recruited participants ranging from 19–65 years old to gain a comprehensive understanding of adulthood. And we include retirees to get more opinions. To hear diverse opinions from the firefighters, we will consider sex, age, job family, region, and years of service. We will explain the objectives and methods of the study, and any potential benefits or disadvantages to participants, and inform them that audio or video of the interview content will be recorded and transcribed. After being thoroughly informed, firefighters who decide to voluntarily participate in the study will complete the written consent form. Participants can be excluded if the researchers judge that it will be difficult for them to participate in the interviews.

### Data collection

We plan to hold the interviews between October 2023 and December 2024. The researchers will collect data through semi-structured interviews using either one-to-one in-depth interviews or focus group interviews (Table 1). This is one of the most common methods of data collection in qualitative studies, and because of its flexible structure, researchers can collect more information from the interview participants, and the participants can also freely express their own opinions [31, 32]. All interviews between researchers and participants will be conducted in Korean. The interviews will last 60–150 min per session, and each individual could participate in up to five interview sessions. The interviews will be conducted in a private space, where the participants can feel comfortable. If in-person interviews are not possible, remote interviews will be held using Zoom. Participants will be asked about their everyday health status, their reason for visiting the hospital, and their experiences and perceptions of KM treatment. With the participants’ consent, audio or video recordings will be made of the interview content. Non-verbal communication during the interview, such as body language or gestures, can be noted by the interviewer in person. In accordance with research ethics regulations, participants will be given appropriate compensation of 100,000 KRW per interview session for participating in the study.

**Table 1 pone.0300532.t001:** Interview guide.

Research questions	Detail questions
Overall experiences of healthcare utilization	1. How is your everyday health? 2. Is there anything you feel is a health problem? 3. What treatment have you received to resolve your health problems? Have you received Korean Medicine treatment? 4. If you have not received treatment or management, why not?
Perceptions and experiences of education or programs provided by the Korea National Fire Agency	1. Do you know what education or programs are provided? 2. Have you received any help? 3. How do you feel about your experiences? 4. If you were the Korea National Fire Agency, what education or programs would you offer?
Perceptions and experiences of Korean Medicine	1. How do you typically feel about Korean Medicine? 2. Are you, or are you not in favor of Korean Medicine? Why? 3. Do you have any experience of Korean Medicine? If yes, what symptoms have you received treatment for? 4. Have your perceptions changed since receiving Korean Medicine treatment? 5. Were you satisfied after receiving Korean Medicine treatment? If you were satisfied/dissatisfied, please explain why? 6. If you have not experience Korean Medicine, why not? 7. What aspects of Korean Medicine do you think should be improved?
Summary of interview content	After summarizing the above interview contents, we will check we have properly understood the participant’s intentions.
Additional content	Is there anything more you would like to talk about?

### Data analysis

The collected data will be analyzed using content analysis, which is a method of analysis in qualitative research, with the aim of understanding phenomena [33]. Content analysis is a valid method that enables specific inferences, based on systematic coding rules, from expansive data collected through interviews [34].

The collected data will be analyzed according to the following procedures:

In the first stage, the researchers will try to understand the overall data. While repeatedly reading the transcribed interview content, the researchers will review, from an objective perspective, which of the participants’ experiences of healthcare utilization are related to Korean firefighters’ perceptions and needs concerning integrative medicine.

The second stage is the process of finding significant statements. Here, the researchers will make sentences from the participants’ interview content, dividing these into analytic units of words, phrases, and sentences. the researchers will then discover significant statements related to Korean firefighters’ healthcare utilization and integrative healthcare and will reconstruct the meaning of these statements.

The third stage is categorization. The researchers will make concepts from the significant statements and combine mutually related or similar concepts to create categories.

In the final stage, the researchers will reorganize the constructed categories into social, personal, and cognitive dimensions.

Before the start of the study, researchers are female doctors of KM (IA, JH) who have learned qualitative research methodology through lectures and writings by qualitative research experts and oversee a research methods and analysis course. All interviews will be discussed by multiple researchers to minimize individual bias. To improve the reliability of the coding process and reflect diverse perspectives, an additional two researchers other than the interviewers will independently evaluate the results through meetings and verify the suitability of the significant statements. One of these additional researchers is a qualitative research expert, not a doctor of KM, and is currently participating in qualitative research education and several qualitative research projects. The additional researcher has PhD in KM and is actively involved in various fields of research, including both qualitative and clinical research. In addition, to increase the reliability and validity of the results, an independent researcher will validate the coding through triangulation.

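### The first analysis stage is aimed at the secondary objective (integrative medicine), and no stage names unmet needs, the primary target

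*Protocol article*

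**What the plan says.** **Objectives.** The primary objective is "to gain an in-depth understanding of the unmet needs of Korean firefighters regarding healthcare utilization", as firefighters themselves see them. It is not limited to any type of medicine. Integrative medicine is the subject of the secondary one: "examine what experiences Korean firefighters have of integrative medicine, obstacles to its use, and how it could help with their unmet needs". It ranks below the first.

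**Study design.** Content analysis is to cover "the state of healthcare utilization by Korean firefighters and their perceptions and needs regarding KM".

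**Data analysis.** There are four stages.
- Stage 1 opens broadly: "In the first stage, the researchers will try to understand the overall data". While rereading the transcripts, the researchers then consider "which of the participants’ experiences of healthcare utilization are related to Korean firefighters’ perceptions and needs concerning integrative medicine".
- Stage 2 breaks the interview content into analytic units and looks for "significant statements related to Korean firefighters’ healthcare utilization and integrative healthcare".
- Stage 3 forms concepts from those statements and groups them into categories.
- Stage 4 is to "reorganize the constructed categories into social, personal, and cognitive dimensions".

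**The concern.** In content analysis, the question put to the text on first reading shapes what the coders later treat as significant. Here that question belongs to the secondary objective. The primary target appears by name in no stage.

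The Introduction says that gaps remain in areas such as rehabilitation and burn care. Suppose a participant describes a gap of that kind and does not connect it with integrative medicine or KM. It falls squarely under the primary objective, but it is not what stage 1 tells the researchers to look for.

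The secondary objective is also affected, because it asks how integrative medicine could help with the unmet needs found. If needs linked to integrative medicine are picked up more readily than others, the set of needs leans towards those that integrative medicine can be said to meet. Its apparent role then looks larger than the interviews would support.

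**Working it through.** No arithmetic applies, and the plan gives no figure to reproduce. The check sets the analysis text against the objectives.

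**1. What each stage is told to look for.**

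| Stage | Topic stated | Names unmet needs? |
|---|---|---|
| 1 | Experiences that bear on views of, and needs for, integrative medicine | No |
| 2 | Healthcare utilization *and* integrative healthcare | No |
| 3 | None (works on the stage 2 statements) | No |
| 4 | None (rearranges the stage 3 categories) | No |

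Unmet needs are named in 0 of 4 stages. Only 2 of the 4 stages state any topic, and these are stages 1 and 2. The needs mentioned in stage 1 are needs concerning integrative medicine, which is a narrower idea than unmet need in using healthcare generally.

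**2. Which objective stage 1 serves.** Set beside the two objectives, the stage 1 question matches the secondary one. The primary objective contains no reference to integrative medicine.

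**3. Whether stage 1 removes anything.** It does not say so. It is described as a reading of all the data, with no rule for setting material aside. Stage 2 starts again from the interview content, not from a subset kept after stage 1.

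**4. Whether stage 2 restores the primary target.** This depends on the *and* in "significant statements related to Korean firefighters’ healthcare utilization and integrative healthcare".
- Read as two separate topics, any statement on healthcare utilization is eligible, and an unmet need with no link to integrative medicine can be coded.
- Read as a joint condition, a statement must concern both, and such a need is not eligible.

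The wording allows either reading. The Study design section lists the two topics side by side, which favours the first. A coder coming straight from the stage 1 question could adopt the second.

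**5. Whether stages 3 and 4 could repair a loss.** They could not. Both work on what stage 2 has extracted, so a need missed there does not return.

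**6. Direction.** The Discussion accepts that having KM practitioners among the researchers could tilt results in favour of KM. The stage 1 question points the same way.

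**The case against.** The strongest reply is that stage 1 is an ordinary familiarisation reading and that coding eligibility is set in stage 2. Stage 2 works from the interview content and names healthcare utilization, the domain in which the primary objective is defined. Table 1 supports this. Its block on experiences of healthcare utilization asks about health problems and about reasons for not getting treatment, and those questions elicit unmet need. On that reading, gaps in rehabilitation or burn care are codable whether or not integrative medicine is mentioned. This stands, and it limits the point to a risk of under-identification.

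A reader might infer something stronger: that stage 1 filters the transcripts, so that needs unrelated to integrative medicine are lost before coding. The document does not support this. It states no exclusion, and stage 2 does not draw on a stage 1 selection.

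A second reply is that safeguards exist. Two researchers who did not conduct the interviews, one of them not a KM doctor, evaluate the results independently, and a further independent researcher validates the coding. These are real protections, but they are described as checks on the statements selected and the coding done. Nothing says that they return to the transcripts to look for needs that were passed over.

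A third reply is that this is a condensed article and the full protocol, supplied as supplementary files, is not shown. Missing coding detail would indeed be no finding, and the absence of the word *unmet* would not be enough alone. The point rests on what the article does state: a stage 1 question that follows the secondary objective.

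**Conclusion.** The point holds as a mismatch between stated texts. The first review of the transcripts is directed only at the secondary objective, and no stage names the primary one. Unmet needs with no link to integrative medicine keep a route into coding through stage 2, so they are not formally removed. They may be under-identified, more so if the stage 2 criterion is read as a joint condition.

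The size of the effect cannot be estimated from the document. What can be counted is that 0 of 4 stages name unmet needs, and that of the 2 stages with a stated topic, one is tied to integrative medicine and the other is ambiguous.

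Two further inferences would go too far. One is that no stage can reach the primary objective: healthcare utilization in stage 2 does cover its domain. The other is that the answer to the secondary objective is settled in advance: the text shows a tilt and its direction, not an outcome.

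The conclusion assumes that the article's stages are the ones the coders will follow, and that the full protocol does not already contain a separate instruction on unmet needs.

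**What to change.** 1. **Stage 1.** Reword it so that the transcripts are reviewed for all experiences of using healthcare and all unmet needs, whether or not they relate to integrative medicine.
2. **Stage 2.** State that a statement on healthcare utilization or unmet need is eligible on its own, and that a statement on integrative medicine is also eligible on its own. This removes the ambiguity of the *and*.
3. **Separate code.** For each unmet need, record whether the participant links it to integrative medicine or KM.
4. **Reporting.** Report the unmet needs with no such link alongside those that have one.

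Arranging the stage 4 categories by objective before applying the three dimensions would help the reader, but it is optional.

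The cost is rewording of the Data analysis section and a modest amount of extra coding. No new interviews, participants or data are needed. If the full protocol already says this, the article only needs to be brought into line with it.

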### Patients’ involvement

In this study, patients will be involved in the whole research procedure, allowing us to collect more abundant, in-depth data. During the interviews, the interview sheet can be adjusted depending on the participants’ experience and preferences. During the interviews, we will communicate with the participants about methods of effectively publicizing our research results and improving their usability.

